**Table 7 Overview of radiation doses during the trial**

|                                                            | Minimum (mSv) | Maximum (mSv)                         |
|------------------------------------------------------------|----------------------|----------------------------------------------|
| Pre-operative CT                                           | 0.60                 | 0.60                                         |
| Peri-operative fluoroscopy                                 | 0.02                 | 0.08 (possible extra fluoroscopy after 3DCT) |
| Peri-operative 3D-CT                                       | 0.38 (2 x 0.19)      | 0.57 (3 x 0.19)                              |
| Post-operative CBCT                                        | 0.20 (4 x 0.05)      | 0.20 (4 x 0.05)                              |
| Total radiation exposure                                   | 1.20                 | 1.45                                         |
| Extra exposure as part of the trial
(Total – Pre-op CT) | 0.60                 | 0.85                                         |

The total radiation exposure for patients included in this trial is between 1.20 and 1.41 mSv (table 7). Since performing a pre-operative CT is part of the standard clinical CI work-up, this means that there is an increased radiation exposure of 0.60-0.81 mSv (depending on the number of 3D-CT's needed intra-operatively) for receiving a CVI compared to receiving a regular CI (regular exposure is around 0.6 mSv). This places the extra radiation exposure associated with this trial in risk category IIa of the International Committee of Radiological Protection (ICRP) (between 0.1 and 1 mSv). For all patients there is a therapeutic effect by taking part in the trial: the CI part of the CVI can be used daily and will lead to increased hearing performance and thus a direct therapeutic effect.

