#### 6.4.3. *Risks related to CVI surgery*

Until now, none of the 13 patients that were implanted with a CVI by the Geneva-Maastricht group suffered from any surgical complications related to the well-defined surgical approach. Risks of surgical implantation are low. Surgery is derived from a frequently performed surgical intervention which has proven to be safe: cochlear implantation. The main risk of CVI surgery is damage to the sensory structures in the cochlea and the vestibular organ, resulting in hearing loss and loss of vestibular function. These risks are minimized by only implanting patients with severe SNHL in the ear to be implanted and

with only minimal vestibular function remaining. Alongside this, the potential hearing loss is compensated for by the CI functionality of the CVI.

The inclusion criteria imply that three types of patients are eligible for participation: patients with BV and bilateral deafness who have an indication for reimbursement of unilateral cochlear implantation (in the Netherlands), patients with BV and unilateral deafness for whom cochlear implantation is not insured (in the Netherlands) and patients with BV and bilateral deafness who have already received a CI in the contralateral ear. Since the CVI is a combined device, combining a VI- and a CI-part in one device (Figure 5), hearing will be restored on the implanted side. Therefore in the first group (bilateral deafness), the CVI will be implanted instead of a regular CI implant during their cochlear implantation in the same surgical field, without additional incisions. The two other groups (unilateral deafness and bilateral deafness with already one CI implanted) will undergo surgery specific for this trial, but will also benefit from the CVI implantation: their hearing will most likely improve .

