### 11.4. Benefits and risks assessment, group relatedness

#### 11.4.1. *Individual patient benefits*

Patients who receive a CVI will benefit from the cochlear part of the device: their hearing will most likely be improved. Patients with bilateral SNHL who do not yet have a CI will receive a CI regardless whether they participate in this trial or not, since for these patients CI implantation is reimbursed by health insurance. Without this trial, unilateral patients would not have received a CI, since a CI is not reimbursed by health insurance in the Netherlands for unilateral SNHL. Also bilateral patients who already have one CI would not have been reimbursed in most cases for receiving a second CI. Therefore, these patient groups have an added individual patient benefit of having the device with CI functionality (i.e. the cochlear part of the CVI) reimbursed by the trial.

Patients will not receive a benefit from the VI part of the device, since it will only be activated during trial-related activities under supervision in the hospital. Because the trial is designed to first investigate the safety and efficacy of chronic daily vestibular stimulation, no promises can be given on the availability of a CVI/AMP device as part of clinical care. However, it would be possible in principle for a combined processor to be developed as an investigational medical device for take-home use by the patient, as a future extension of this study. Both the manufacturer of the device and the principle investigator intend to pursue this study extension towards home-use when the mid-term results look favorable towards a safe and effective intervention. In other words: the implanted part does not have to be explanted and might still be used in the future.

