In standard clinical practice, patients that undergo retro-auricular ear surgery receive a preoperative CT scan of the mastoid to inform the surgeon about individual anatomy. We will perform the same pre-operative scan used in standard clinical CI practice as part of the pre-operative assessment for our VCI surgeries. This pre-operative CT will also be fused with the 3D-CT to assess electrode placement pre-operative (cfr. Infra). The resulting radiation dose from this CT scan is 0.6 mSv. To assess the right insertion depth of the electrodes into the SCCs, a fluoroscopy-based technique is used. Fluoroscopy consists of making real-time x-ray images of, in this case, the inner ear. Within the image created by using fluoroscopy, the electrodes are visualized within the SCCs in real-time, allowing for fine-tuning the placement of the electrodes in the SCCs. In previous research, the fluoroscopy-based technique was developed and optimized, resulting in an efficient work-flow only requiring between 0.019 and 0.042 mSv to achieve a significant improvement in electrode placement accuracy. Within this pilot study, a substantial improvement was achieved over "blind" insertion, resulting in 94% of the electrodes being placed within the desired distance to the target.

After using the 2D guidance of fluoroscopy to insert the electrodes in the SCC's, an intra-operative 3D-CT of the head will be made to verify the exact location of the electrodes (distance to the ampulla) in 3 dimensions. We namely will fuse the 3D-CT image onsite with the pre-operative CT mastoid (free of scattering by the electrodes), allowing us to improve the accuracy of electrode placement even further. If

deemed necessary, repositioning of the electrodes will be performed using fluoroscopy guidance and if necessary second 3D-CT is used to register the position of the repositioned electrodes. A final 3DCT is made after fixation of the electrodes. The radiation dose of the intra-operative 3D-CT has been calculated and was found to be low, only 0.19 mSv per scan.

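### Section 13.1.11 states lower maximum radiation figures than Table 7, and its risk category is not shown to hold for patients whose pre-operative CT is made only because of the trial

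*Protocol*

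**What the plan says.** Protocol section 13.1.11 builds the exposure from four sources.

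- Pre-operative CT: "The resulting radiation dose from this CT scan is 0.6 mSv".
- Fluoroscopy: a workflow "only requiring between 0.019 and 0.042 mSv". Table 7 gives a minimum of 0.02 mSv and a maximum entered as "0.08 (possible extra fluoroscopy after 3DCT").
- Intra-operative 3D-CT: "only 0.19 mSv per scan", with two or three scans.
- Post-operative CBCT: four scans at 0.05 mSv.

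Table 7 totals these to 1.20 to 1.45 mSv. Its last row takes off the pre-operative CT and reports 0.60 to 0.85 mSv as the extra exposure belonging to the trial.

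The paragraph under the table refers to it but reads: "The total radiation exposure for patients included in this trial is between 1.20 and 1.41 mSv". It gives the increase over a regular CI as 0.60 to 0.81 mSv, on the ground that the pre-operative CT belongs to the usual CI work-up. It continues: "This places the extra radiation exposure associated with this trial in risk category IIa of the International Committee of Radiological Protection", and prints the range of that category as 0.1 to 1 mSv.

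On the eligible patients, section 6.4.3 names three types. One would have a CI in regular care. Of the rest it says: "The two other groups (unilateral deafness and bilateral deafness with already one CI implanted) will undergo surgery specific for this trial". Section 11.4.1 adds: "Without this trial, unilateral patients would not have received a CI". It also says that patients who already have one CI would mostly not be reimbursed for a second. Section 11.6 repeats that both groups receive something insurance would not otherwise cover.

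**The concern.** There are two separate issues.

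First, the text and the table disagree on the maximum, although the text cites the table as its source. Section 8.3.4 sends the reader to 13.1.11 for total exposure, so the section should give one answer.

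Second, the comparator changes between two consecutive sentences. The extra exposure is calculated against receiving a regular CI. The category sentence then treats the same number as the exposure associated with the trial, and the last row of Table 7 is labelled in the same way. The two quantities are equal only for a patient who would have had the pre-operative CT without the trial. For a patient who would not, subtracting the CT removes exposure that the trial itself causes.

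At stake is the category on which the radiation justification rests. The CT is the largest single component in Table 7, so whether it is counted decides on which side of the printed 1 mSv limit a patient falls.

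**Working it through.** **Inputs, all from section 13.1.11 and Table 7 (mSv)**

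| Component | Minimum | Maximum |
|---|---|---|
| Pre-operative CT | 0.60 | 0.60 |
| Fluoroscopy | 0.02 | 0.08 |
| 3D-CT, 0.19 per scan | 2 × 0.19 = 0.38 | 3 × 0.19 = 0.57 |
| CBCT, 0.05 per scan | 4 × 0.05 = 0.20 | 4 × 0.05 = 0.20 |

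**Step 1. Does Table 7 add up?**

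- Minimum total: 0.60 + 0.02 + 0.38 + 0.20 = 1.20.
- Maximum total: 0.60 + 0.08 + 0.57 + 0.20 = 1.45.
- Extra, without the CT: 1.20 − 0.60 = 0.60 and 1.45 − 0.60 = 0.85.

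The table is internally correct.

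**Step 2. Can the text figures be reproduced?**

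The minima (1.20 and 0.60) agree with the table. The maxima do not follow from it. They appear when fluoroscopy is entered once at its upper value, 0.042 rounded to 0.04:

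- 0.60 + 0.04 + 0.57 + 0.20 = 1.41.
- 1.41 − 0.60 = 0.81.

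The table's 0.08 corresponds to two sessions: 2 × 0.042 = 0.084, rounded to 0.08. On this reconstruction the text counts the third 3D-CT but not the second fluoroscopy session. The difference is 1.45 − 1.41 = 0.04, and likewise 0.85 − 0.81 = 0.04. The reconstruction is an inference, because the protocol does not explain how 1.41 arose.

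**Step 3. Does the mismatch alone affect the category?**

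No. Both 0.81 and 0.85 lie between 0.1 and 1 mSv.

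**Step 4. Exposure attributable to the trial, by whether the CT would have been made anyway**

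Trial-attributable exposure = total − doses the patient would have received without the trial.

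| Patient | CT subtracted? | Exposure (mSv) | Against the printed 0.1 to 1 mSv |
|---|---|---|---|
| Would have a CI in regular care | Yes | 0.60 to 0.85 | Inside |
| Implanted only because of the trial, usable CT already available from regular care | Yes | 0.60 to 0.85 | Inside |
| Implanted only because of the trial, CT made for the trial | No | 1.20 to 1.45 | Above, even at the minimum |

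The second row follows from section 8.3.6 (Inclusion): CI eligibility tests already done in regular care are not done again. The third row follows from the same section, which places the MRI and CT within the inclusion procedure, together with the descriptions of the patient groups in 6.4.3, 11.4.1 and 11.6.

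**The case against.** The protocol names its comparator. The sentence giving the increase compares a CVI with a regular CI and, apart from the 0.04 mSv, is right. The full dose is also not concealed: 1.20 to 1.45 mSv is the total row of Table 7, shown for everyone.

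There is also a clinical argument. Section 4.2.2 requires CI candidacy in the ear to be implanted. Section 13.1.11 describes the CT as the scan used in standard CI practice, and it says every participant gains a therapeutic effect through daily CI use. On that view the CT is work-up for a useful hearing device. Finally, section 4.2.3 gives preference to patients who qualify for a regular CI, so the affected group may be small.

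Most of this stands as a limit on the point, but it does not remove it. The comparator is stated for the increase and then dropped in the category sentence and in the label of the table's last row. Benefit can help to justify an exposure, but it does not change its size or the printed bound. A preference for one group does not exclude the other two.

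A reader might infer that category IIa is wrong for every patient implanted only because of the trial. The documents do not support this. Those with a usable clinical CT stay at 0.60 to 0.85 mSv, and for patients with one CI the protocol says only that a second would mostly not be reimbursed. Nor can one infer that the patient information carries wrong figures, since it is not shown.

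**Conclusion.** The point holds in a conditional form.

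The disagreement between text and table is certain and small: both maxima in the text are 0.04 mSv below Table 7, with no effect on the category.

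The category statement is too broad. It is supported for patients who would have the pre-operative CT without the trial. It is not supported for a patient who would not otherwise be implanted and whose CT is made for the trial. For that patient the protocol's own doses give 1.20 to 1.45 mSv, which is 0.20 to 0.45 mSv above the 1 mSv limit.

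This rests on three assumptions: the component doses are as printed, the category range is as printed, and at least one enrolled patient meets the condition. The protocol does not say how many will. It also does not give the category above 1 mSv, so none is asserted here. Nothing here shows that the exposure is unacceptable. The finding is that the stated justification does not cover every eligible patient.

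**What to change.** In section 13.1.11:

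1. Reconcile the paragraph with Table 7. With the table's components it should read 1.20 to 1.45 mSv total and 0.60 to 0.85 mSv extra. Label the second range, in the text and in the table's last row, as the difference from a regular CI.
2. Add one line giving 1.20 to 1.45 mSv as the trial-attributable exposure for patients whose pre-operative CT is made only because of the trial.
3. Limit the IIa statement to patients who would have the CT anyway, and re-assess the category for the others.
4. Check that the patient information carries the same figures.

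The cost is a few sentences and a re-assessment of the category. A stated risk figure becomes less favourable for some patients. No scan or procedure changes.

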#### 13.1.12. *Risks related to the tests included in the trial*

The tests included in this study are: VOR tests, VSR tests, tests of vestibular perception, a gait analysis, hearing tests and questionnaires. All these tests are routinely used in our clinic and research practices, and have proven to be safe .

Semi-structured qualitative interviews will be conducted and involve patient expectation and patient experiences when being part of the trial. The team of researchers will explicitly consider the personal limits of the patients, as will be done during all trial related activities.

The tests included in this study are: VOR tests, VSR tests, tests of vestibular perception, a gait analysis, hearing tests and questionnaires. All these tests are routinely used in our clinic and research practices, and have proven to be safe .

#### 13.1.13. *Risks related to the COVID-19 epidemic*

Due to the uncertainty of how long the government-mandated security measures to prevent the spread of the COVID-19 virus will maintain active, all trial related procedures will be made COVID-19 safe for as long as necessary. The COVID-19 rules set up by the MUMC+ will be used as a guideline in order to maintain a safe environment for both patients and staff. For most of the trial activities (especially during the first year of the trial) including tests, surgery and CI rehabilitation there are already COVID-19 safe procedures in place. For trial-specific procedures such as during the fitting and prolonged stimulation periods, standard operating protocols will be written which ensure a safe distance of 1,5 meters between the different people involved and/or provide personal protective equipment (facemasks, disinfectants) to prevent spreading of the virus. Conforming to MUMC+ policy, it will be ensured that the execution of this trial will not have an influence on the regular clinical care which is provided by the hospital.

Decisions on starting, stopping and restarting of the trial will be based on the MUMC+ guidelines. If it were to happen that medical research is not allowed for a certain period due to a wave of infections, or a patient is required to be in home-quarantine at the time a trial activity is planned, this will never lead to an unsafe situation for the patient. None of the trial-related activities which are not also part of clinical care are essential for maintaining the patient's safety. Therefore all these activities can be postponed without safety-concerns.

The only risk related to a change in schedule due to COVID-19 would be that data-quality might be negatively affected. Since most time points in the study are flexible, this will only be a problem if it occurs during a prolonged stimulation period, which will be at least 1,5 years after the start of the trial. By that time it is highly likely that either a vaccine or a treatment will have been developed which removes the risk of such a temporary halt influencing data quality.

### 13.2. **Synthesis**

The main risks which are associated with the implantation and use of the CVI are associated with damaging the sensory structures in the inner ear, resulting in reduced vestibular and auditory response. These risks are mitigated by implanting only patients with severe BV and severe SNHL in the ear to be implanted, meaning these patients have almost no residual function left which can be damaged.

Any other risks associated with the CVI, as described in chapter 6.4 and 13.1, are minimal and similar to receiving a CI. Any risks associated with using the VI part of the CVI are reduced by allowing the stimulation to be stopped immediately by the patient themselves by turning off the AMP or removing the transmitting coil from their head. Alongside this, there will always be a member of the research team present when the VI part of the CVI is active.

According to our opinion, the risk mitigation strategies implemented in the trial result in acceptable risks for the patients participating in this trial.

